## Abstract

**Background:**

Odontoid fractures of the second cervical vertebra commonly affect elderly patients due to osteoporosis and low-energy trauma. Treatment is controversial, with prolonged cervical collar immobilization risking non-union and complications, and surgical C1–C2 stabilization involving higher upfront surgical risks. High-level evidence from randomized controlled trials to guide optimal treatment decisions is lacking. The SCORE study aims to determine whether surgical stabilization is non-inferior to conservative collar management in maintaining functional independence for elderly patients with unstable odontoid fractures.

**Methods:**

SCORE is a multicenter, parallel-group, randomized controlled non-inferiority trial enrolling 322 patients aged ≥70 years with acute (≤2 weeks) unstable odontoid Type II, III, or atypical fractures. Participants will be randomized 1:1, stratified by center, to receive surgical stabilization via posterior C1–C2 fixation or conservative management with a rigid cervical collar. The primary outcome measure is the change in Barthel Index (BI) from baseline to 12 weeks. Secondary outcomes include quality of life (EQ-5D), neck pain (Visual Analog Scale, VAS), neck disability (Neck Disability Index, NDI), radiographic fusion, treatment compliance, cross-over rates to surgery, and incidence of adverse and serious adverse events up to 6 months. Follow-ups will take place at 12 weeks and 6 months post-injury, with an additional visit at approximately 2 weeks post-surgery for surgical patients. Analysis will use mixed models for repeated measures, targeting 90% power to detect non-inferiority within a 5-point margin on the BI (one-sided α = 0.025), accounting for 15% attrition.

**Discussion:**

This trial addresses a critical evidence gap by directly comparing surgical and conservative treatments, aiming to guide clinical decision-making and improve functional outcomes and quality of life in elderly patients.

**Trial registration:**

ClinicalTrials.gov, ID: NCT06961578

## Background and rationale

Odontoid fractures (OF) are among the most common injuries of the spine and are becoming “endemic” in the geriatric population. As opposed to a younger population in which these fractures occur after high velocity trauma and need to be treated differently, it is now clear by evidence that C2 fractures in the elderly population are insufficiency fractures due to osteoporosis [1,2]. OFs occupy a large volume of our health care system in everyday clinical practice. They continue to gain relevance considering the increasing life expectancy of the aging population, which is particularly susceptible to prolonged morbidity, functional disability, and impaired health-related quality of life [3–7]. Controversy exists as to the optimal treatment, weighing potential failure with external collar bracing against a surgical intervention in an elderly patient [8,9]. As of today, no high-class evidence comparing surgery with conservative bracing in the geriatric population exists and guidelines do not offer clear-cut recommendations as to the optimal treatment [10]. In addition, secondary sequelae of the conservative regimen such as insufficient fracture healing, prolonged pain, deep vein thrombosis and even neurological injury are often underreported and misjudged in clinical practice, oftentimes necessitating secondary surgical stabilization in patients with an impaired general condition [3,11]. OFs occur in 25% of all cervical spine injuries in Germany and Western regions, while in patients older than 65 the incidence is double as high, with OF being the most common cervical spine injury [12]. Geriatric patients are predisposed to OF because of osteoporosis and a propensity to fall. Mortality reaches up to 44% at an average of 2 years after suffering an OF [13,14]. Osteoporosis, a poor blood supply of the fracture gap, and age-associated impaired biomechanics lead to disrupted fracture healing, resulting in an increased non-union rate of up to 85% [5,15–18]. Regardless of the applied treatment, fractures in the elderly bear a high risk of poor outcome and mortality due to co-morbidities and immobilization [19]. The primary goal of therapy is to achieve the fastest possible restoration of pre-traumatic mobilization. The current standard of care treatment consists of either collar bracing of the cervical spine for at least 12 weeks or surgical posterior stabilization with a screw-rod-construct [7,15,20–23].

### State of research

One large prospective non-randomized international registry study, INNOVATE (leadership: Leiden University Netherlands), is underway to assess fracture healing and outcome after surgical vs. conservative treatment of OFs in the elderly [24]. According to the interim analysis of INNOVATE (Huybregts et al., Age and Ageing 2024), no outcome differences were observed between surgical and conservative arms [25]. INNOVATE has defined a radiographic parameter as primary outcome, in addition to the NDI, which has been conceived and validated for the general population without specific aspects for elderly patients. Another randomized clinical trial, the Uppsala Study on Odontoid Fracture Treatment (USOFT; leadership: Uppsala University Hospital Sweden) is still recruiting since its registration in 2016. The study group also chose the NDI as primary outcome parameter, they have, however, excluded demented patients and aim for only 50 patients over both surgical and conservative arms for a statistical power of 80% [26].

### Rationale for the project

We designed our clinical study with the BI as primary outcome to focus on the health-related autonomy in the elderly, specifically including demented patients and patients incapable of giving consent. We aim to answer the principal question of how geriatric patients with substantial comorbidity and frailty can return to their prior level of autonomy and activity after suffering an OF [9]. While we concur that the NDI is suitable for use in the general population, we believe the BI is more adequate to cover the special needs of the elderly [19,27–29]. Our choice of the BI as a primary outcome and NDI as a secondary outcome measure has been proposed after consulting with patient representatives and advocacy groups (Bundesselbsthilfeverband für Osteoporose e.V. (BfO), Selbsthilfe Landesverband für Osteoporose Bayern e.V. (LfO) and Osteoporose Selbsthilfegruppen Dachverband e.V. (OSD), who communicated a need for a measure that is more accessible and relevant in everyday practice [30–36]. This, in conjunction with the shortcomings of available literature and lack of current studies, warrants the conduct of this confirmatory clinical study to expand on the preceding retrospective investigations and provide high quality scientific evidence for clinical decision-making. It must be noted that the geriatric population is drastically underrepresented in published literature, since clinical trials generally eschew this population in particular [37].

## Methods

This is a two-arm, prospective, multi-center, open-label, randomised, controlled non-inferiority clinical study in a parallel group design.

The study compares two established standard methods against each other regarding their efficacy in terms of functional status on follow-up. To date, there is no scientific equipoise concerning the treatment options for OFs, these being surgical stabilization or external collar bracing [4,6,13,38,39]. Hence, both arms are considered as interventions: experimental intervention = surgical group undergoing posterior instrumentation, control intervention = conservative group subjected to external collar bracing.

The clinical study complies with the SPIRIT guidelines and has been approved by the local ethics committee (No. 2024-630-S-NP). The study was registered in clinicaltrials.gov (https://clinicaltrials.gov/study/NCT06961578) prior to the inclusion of the first patient.

### Study population

The target population consists of patients with unstable odontoid fractures types II or III as classified by Anderson and d’Alonzo, and atypical C2 fractures. The planned sample size is 322 patients. Fig 1 depicts the study timeline of events.

**Fig 1 pone.0337999.g001:**
[figure not shown]
SPIRIT 2025 enrolment flow chart and study timeline [47].

### Inclusion criteria

At least 70 years oldAcute unstable OFs (types II, III as classified by Anderson and d’Alonzo, and atypical)Less than two weeks post injuryWritten informed consent

### Exclusion criteria

Previous treatment for odontoid fractureConcomitant fractures of the subaxial cervical spine necessitating surgerySignificant comorbidity resulting in inoperability of the patient: i.e., ASA score > 4Neurological compromise due to displaced fracture

### Measures taken (surgical and conservative treatment)

The surgical intervention is a surgical fracture stabilization with a posterior screw-rod system and represents an established surgical treatment according to standard of care for OFs [3,13,14,20,40,41]. The routine surgery commonly lasts approximately 100 minutes and requires a hospital stay of about 6 days [42,43]. An additional external bracing in the postoperative setting is not required. The surgery is tailored specifically towards geriatric insufficiency fractures of the odontoid, which makes stabilization with a screw-rod-construct from a posterior approach a necessity to achieve adequate stability for this patient population. We deliberately exclude the possibility to conduct an anterior fusion by odontoid screw fixation as described by Böhler, which has been shown to be a biomechanically insufficient treatment particularly in geriatric patients [6,15,23,44,45].

The conservative intervention also aims for immobilization, but via an external collar. A typical detriment of the conservative intervention in everyday practice stems from its absolute reliance on the patient’s compliance to wearing the collar permanently for at least 12 weeks, which considerably challenges this treatment strategy [22]. This compliance problem is highly relevant to the treatment outcome, although data on compliance rates in the elderly are fairly scarce [17,44,46]. We are aware that the regularity of wearing the brace cannot be verified with certainty, and in probably the majority of cases the collar is not worn permanently against the physician`s recommendation due to relevant side effects. Therefore, the adherence to therapy will be assessed via a patient diary in which the hours of wearing the collar will be documented. However, this will reflect the everyday reality and belongs to a real-life representation of the conservative therapy regimen.

Over the course of this study, patients of the conservative group can undergo surgical intervention, if requested by the patient or advised by the treating physician, until week 12. Prior to this crossover surgery, patients are required to attend the crossover visit. After surgery, the patients will be invited to Visit 2 at discharge or 14 days post-surgery at the latest, and to Visit 4 at 6 months.

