VAS Neck Pain: A standardized instrument for assessing neck pain on a continuous, visually coded scale that is used in routine clinical practice.

Neck Disability Index (NDI)): A questionnaire used to measure neck-specific disability for both groups, constituting the secondary outcome.

Concomitant medications: Categorized by substance class; antidiabetics, anticoagulants, antithrombotic medicine, antiosteoporotic agents (vitamin D3, calcium, bisphosphonates), medication for movement disorders (e.g. Parkinson’s disease, etc.), antidepressants, steroids, and “other”.

Adverse Events (AEs): Monitoring of all AEs and documentation at each visit, with particular attention to safety-relevant adverse events of special interest (AESIs) and serious adverse events (SAEs).

Duration of Surgery: Time taken to complete the surgery (surgical group or cross-over).

Patient or caregiver diary: diary for patients to document daily duration of cervical collar wearing (conservative group).

Readmission to Hospital: Recording if the patient is readmitted to the hospital any time during the study until week 12, i.e., for the management of medical or surgical complications of either treatment.

Crossover to Surgical Group (see crossover visit): Noting if the patient switches from the conservative to the surgical arm due to failure of conservative treatment until week 12. In case of crossover and conduction of surgery, documentation of visits 1 (surgery), 2 (discharge) and 4 (6 months), after which the study concludes for the crossed patient.

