### Statistical analyses

Analysis will be performed on all patients who were randomized to the study. The primary estimand and its attributes are described in Table 1.

**Table 1 pone.0337999.t001:** Definition of all five attributes used to construct the primary estimand for the SCORE study (non-inferiority setting).

Primary estimand	
**Population**	Geriatric patients with recent type II & III odontoid fractures (as defined by trial inclusion/exclusion criteria).
**Variable**	Functional status accessed as the change in Barthel Index (BI) between baseline and 12 weeks thereafter
**Treatment**	• Surgical stabilization C1-2 by dorsal screw-rod construct (duration of treatment: Approximately 100 min + approximately 6 days hospital stay) or • Conservative therapy by external cervical collar immobilization (duration of treatment: 12 weeks)
**Population-summary measure**	Mean difference, including 95%CI.
**Intercurrent event (IE) and strategy**	• Refusal of therapy as randomized – multiple imputations (hypothetical estimate) • Crossover from the conservative to the surgical arm after randomization but before week 12 – use the last available BI value before surgery as best estimate of the hypothetical BI value at week 12 *Note: Cross-over from the conservative to the surgical arm after week 12 is allowed, as it does not influence the primary variable, which is measured at week 12* • Loss to follow-up after start of therapy – multiple imputations; missing at random assumed • Death – (expected ca. 10%) multiple imputations (hypothetical estimate)

Intercurrent events (IEs) will be dealt with using a hypothetical strategy to determine the treatment effect without the abovementioned IEs.

The primary endpoint will be tested using a mixed model for repeated measures (MMRM) of BI, where treatment, time, their interaction, baseline BI scores, age, and CCI will be fixed covariates, and study center will be a random covariate. In case the model does not converge due to small centers, the covariate center will be abandoned. The adjusted mean difference between groups in the primary outcome will be tested at the 12-week time point.

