Primary and secondary analyses will use all available data at the pre-determined time points. The extent of missing data will be calculated at each time-point. Patients with missing data at the 3-month time point will be compared to those who participated in all visits. Variables asso-ciated with missing data and baseline characteristics will be included as covariates in the mixed model as a further sensitivity analysis of the primary endpoint. Additionally, multiple im-putations will be used on data for each outcome measure at each time point. The results will be presented as adjusted mean or percentage and treatment effect including 95% CI from the 10 iterations.

No interim analysis for efficacy is planned, so the study will continue until full enrolment is reached or unless stopped early for safety or futility by recommendation of the SMB.

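### Patients who cross over to surgery have no scheduled 12-week Barthel Index, which leaves the planned as-treated analysis and any as-randomised check without observed values for them

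*Protocol article*

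**What the plan says.** All references are to the protocol article.

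- **Who crosses over.** Measures taken (surgical and conservative treatment) states that "patients of the conservative group can undergo surgical intervention, if requested by the patient or advised by the treating physician, until week 12". No crossover in the other direction is described.
- **Before surgery.** "Prior to this crossover surgery, patients are required to attend the crossover visit". The visible text does not say whether the BI is recorded there.
- **After surgery.** The same section says that "the patients will be invited to Visit 2 at discharge or 14 days post-surgery at the latest, and to Visit 4 at 6 months". The crossover entry under Data to be collected asks for "documentation of visits 1 (surgery), 2 (discharge) and 4 (6 months), after which the study concludes for the crossed patient".
- **General schedule.** The Abstract says: "Follow-ups will take place at 12 weeks and 6 months post-injury".
- **Primary variable.** Table 1 under Statistical analyses defines it as the "change in Barthel Index (BI) between baseline and 12 weeks thereafter".
- **Crossover in the primary estimand.** For crossover before week 12, Table 1 says to "use the last available BI value before surgery as best estimate of the hypothetical BI value at week 12".
- **Sensitivity analysis.** The statistical text printed under Research ethics approval and consent repeats the primary analysis as treated, with every operated patient, crossovers included, placed in the surgical group. The text that follows adds: "Primary and secondary analyses will use all available data at the pre-determined time points".

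**The concern.** The trial's one primary measurement is the BI at 12 weeks, and the visit schedule drops it for a group of patients defined by what happened to them after randomisation. The group exists in the conservative arm only. It is related to outcome, since the crossover entry ties the switch to failure of conservative treatment.

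In an open-label non-inferiority trial with a hypothetical primary estimand, a reader will want to see whether the result survives when patients are compared as randomised with the values they actually had at week 12. The sponsor has also planned an as-treated analysis. Both need a week-12 BI after crossover surgery. Once week 12 has passed for a patient, that value cannot be collected.

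**Working it through.** **1. Is Visit 3 the 12-week visit?** The figures with the visit table are not shown, so this is inferred. Follow-up is at 12 weeks and 6 months. Visit 2 is the early postoperative visit and Visit 4 is the 6-month visit. Visit 3 lies between them and carries the CT that assesses fracture healing. No other reading fits the text.

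**2. Is the omission deliberate?** Two places list the visits after crossover. One names Visits 2 and 4. The other names Visits 1, 2 and 4 and then ends the study for that patient. A closed list given twice is a stated rule, not a result of condensing the protocol.

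**3. What each analysis needs from a crossover patient**

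| Analysis | Value needed at week 12 | Available under the schedule? |
|---|---|---|
| Primary (hypothetical strategy, Table 1) | Last BI before surgery, carried to week 12 | Yes; at worst the baseline BI |
| As treated (planned sensitivity analysis) | BI after surgery, counted in the surgical group | Not observed |
| As randomised on observed data (not described in the article) | BI after surgery, counted in the conservative group | Not observed |

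If the as-treated analysis keeps the Table 1 rule, it enters a BI recorded during collar treatment as a surgical outcome. If it drops the rule, the value must be imputed. Neither is an observed outcome after surgery.

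**4. How many patients**

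Inputs from Sample size calculation: 137 evaluable patients per group and 15% drop-out. The stated arm size reproduces: 137 / (1 − 0.15) = 161.2, given as 161 per arm; 274 / 0.85 = 322.4, given as 322.

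The documents state no crossover rate c, so c is assumed. Patients affected = c × 161:

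- c = 5%: 8.1, about 8
- c = 10%: 16.1, about 16
- c = 20%: 32.2, about 32
- c = 30%: 48.3, about 48

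The Background says that conservative care often ends in later surgery, and the Discussion cites failure in 50–60% through non-compliance where nursing support is lacking. Neither is a crossover rate for this trial. The 10–20% used here is a working assumption.

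**5. Share of the as-treated surgical group.** Suppose all 161 patients randomised to surgery are operated on, and ignore drop-out. At 10% crossover the group is 161 + 16 = 177, and 16 / 177 = 9.0% have no observed week-12 BI. At 20% it is 161 + 32 = 193, and 32 / 193 = 16.6% have none.

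**The case against.** The strongest reply is that the schedule follows from the estimand. Table 1 names crossover before week 12 and sets a hypothetical strategy for it. A BI taken at week 12 after crossover surgery would be set aside in the primary analysis even if it were collected. This stands: the primary analysis as defined does not need the missing value.

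Three further replies have some force.

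- **Other BI values may exist.** The crossover visit or Visit 2 may include the BI, and a patient operated on shortly before week 12 would have Visit 2 close to that date. The figures that would show this are missing. But neither visit is the 12-week assessment, and for an early crossover neither is near it.
- **Imputation is planned** for each outcome at each time point, so an as-treated estimate can be computed. For crossovers it would rest on a model throughout, with no observed week-12 values from such patients to inform it.
- **A treatment-policy analysis is not described in the article.** True, so its absence contradicts nothing there. The as-treated analysis is planned, and the gap affects it directly.

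A reader might go further and infer that the primary analysis fails, or that its power drops because crossovers count as missing. The documents do not support this, since these patients contribute a carried-forward value. A reader might also blame the visit schedule for bias in the primary result. Any such bias comes from the carry-forward rule; collecting the week-12 BI would not remove it, but would allow an observed comparison beside it.

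**Conclusion.** The point holds in a limited form. Two places in the protocol article leave out the 12-week BI for patients who cross over, and these patients arise only in the conservative arm. The primary analysis can run. The planned as-treated analysis has no observed week-12 BI after surgery for exactly the patients whom it reclassifies. A primary result that rests on a carried-forward value in one arm cannot be checked as randomised on observed data.

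About 16–32 of 161 conservative patients would be affected at an assumed crossover of 10–20%; the true rate is unknown. The conclusion rests on Visit 3 being the 12-week visit, and on the two written lists being complete. If a figure that is not shown does schedule Visit 3 for crossovers, it contradicts both lists and they must be reconciled. The loss is avoidable but cannot be reversed later, which is the reason to act before patients reach week 12.

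**What to change.** 1. In Measures taken and in the crossover entry under Data to be collected, keep the Visit 3 BI at 12 weeks for every randomised patient, crossovers included. Allow telephone or caregiver report where a visit is not feasible.
2. Use the same time origin for everyone. The Abstract counts follow-up from injury and Table 1 counts from baseline, so state which applies.
3. Use the observed values in the as-treated analysis, and state that the Table 1 carry-forward value is not used there.
4. Pre-specify a treatment-policy (as-randomised) analysis with the observed values, reported beside the primary analysis as supportive. The non-inferiority claim need not depend on both: that would be a new decision rule with a loss of power that has not been worked out.

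The hypothetical strategy can stay as the primary analysis. The sample size remains 322 and no treatment rule changes. The cost is a short amendment and one extra BI contact per crossover patient, or about 16–32 contacts over the whole trial at the assumed rates.
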